### 12.4 AE/SAE Reporting

AE/SAE will be documented at each clinic visit starting at visit 3. Information on adverse effects will be determined at each clinic visit by direct questioning of the subjects, vital signs, clinical assessment, laboratory test, and by interval telephone evaluations starting 1 week after the first infusion using a set of questions to identify symptoms or signs related to an adverse event and will continue through the rest of the study.

The PI, with the assistance of her study team, will be responsible for the detection and documentation of events meeting the criteria and definition of an AE or SAE as provided in this protocol. For each AE and SAE, the PI will make an assessment of:

1. The severity grade (CTCAE criteria).
2. The duration (start and end dates or if continuing at the Safety Follow-up Visit).
3. Its relationship to the study treatment (Reasonable possibility that AE is related: No, Yes).  
The investigator will use clinical judgment to determine the relationship, alternative causes (e.g. the natural history of an underlying disease, concomitant therapy, other risk factors), and the temporal relationship of the AE to the infusion procedure will be considered and investigated.
4. Action taken with respect to study or investigational treatment (none, dose adjusted, temporarily interrupted, permanently discontinued, hospitalized, unknown, not applicable).
5. Whether medication or therapy was given (no concomitant medication/non-drug therapy, concomitant medication/non-drug therapy).

6. Outcome (not recovered/not resolved, recovered/resolved, recovering/resolving, recovered/resolved with sequelae, fatal, unknown).
7. Whether it is serious, where a serious adverse event (SAE) is defined as in Section 12.2.

All Adverse events that meet all three definitions described above of a Suspected (related or possibly related to study drug or participation in the research), Unexpected and Serious Adverse Reaction (SUSAR) must be reported as soon as possible but no later than 7 calendar days after the investigator's initial receipt of the information, to the University of Texas Health Science IRB and the FDA. If the SUSAR report involves the death of a participant, the event needs to be reported to IRB/FDA within 24 hours after first knowledge by the investigator via facsimile or email or by telephone. Annually a list of all AEs & SAEs will be compiled in an approved format and will be submitted to the FDA as part of the IND Annual FDA Report.

### 12.5 Follow-up AEs and SAEs

All AEs and SAEs documented at a previous visit and designated as on-going, will be reviewed at subsequent visits until resolved or at the time of the subject's end of study participation. All SAEs that the primary investigator determines is related to the study will be followed until resolution, until the condition stabilizes, until the event is otherwise explained, until the subject is lost to follow-up or until the patient has completed their study follow up period. Once resolved, the appropriate AE/SAE forms page(s) will be updated in the CRF and the IRB will be updated as appropriate.

## 13. Study Modification/Discontinuation

The study may be modified or discontinued at any time by the IRB, the DSMB or the FDA as part of their duties to ensure that research subjects are protected

### 13.1 Subject Withdrawal or Termination

Subjects' participation is considered complete after the final visit at 78 weeks. However, subjects may withdraw from the study at any time for any reason, without any consequence.

In addition, a subject may be withdrawn from the study by the investigator for reasons including the following:

1. Lost to follow-up
2. Adverse Event (AE) or Serious Adverse Event (SAE)
3. Patient choice (withdrawal of consent; the investigator will attempt to ascertain reason)
4. Protocol violation/non-compliance

5. Investigator's decision to terminate the study
6. Development of a new co-morbid neurological, medical or psychiatric disorder that interferes with the measurement of disease progression.

Subjects are free to withdraw at any time. The primary reason for withdrawals from the study will be recorded in the study exit form. Subjects who withdraw or are withdrawn will be encouraged to complete an Early Termination Visit. Although subjects are free to withdraw at any time, subjects will be encouraged to remain in the study for follow-up evaluations. Subjects who withdraw will be discontinued from all study procedures and will be encouraged to return to their primary neurologist for follow-up care.

### 13.2 Lost to Follow-up

If a subject fails to appear for any visit, three attempts on separate occasions will be made by telephone and/or e-mail to contact the subjects, if there is no response this should be followed by a certified letter to the last known address. The contact attempts will be recorded on the study exit form. Every effort will be made to determine the subject's health status and document the subject outcome if possible.

### 13.3 Screen Failures

Screen Failures are defined as any patient who has been consented but fails to continue to meet inclusion/exclusion criteria prior to the MSCs infusion. Any patient that discontinues the study subsequent to the infusion will be a study patient withdrawal.

## 14. Statistical Considerations

Bayesian Statistical Methods. Developing effective neurological interventions requires incremental improvement of theoretically sound treatments based on systematically accruing data. Indeed, addressing the so-called "Pipeline Problem" in developing clinical applications, the FDA has indicated that Bayesian statistics offers one avenue for improved methodological efficiency. Decision-making based on an initial treatment trial is assisted by estimates of the probability of an effect of some specified magnitude. These statements, not part of the conventional, Frequentist statistical lexicon, are accessible via Bayesian approaches, particularly with small sample sizes.

## 14.1 Blinding and Randomization

This is a double-blind placebo-controlled study. Subjects and site personnel will be blinded to the randomization assignment except for one study person who will be authorized to randomize and keep the blind (or break the blind if needed). Subjects will be randomized to receive any of the 3 treatment arms in 1:1:1 ratio using a computer table randomization method by the statistician prior to the blinded study treatment.

## 14.2 Sample Size:

Having demonstrated the safety of MSC Therapy in a previous study, sample size justification will focus on Hypothesis 1.1. Schulman et al define small, medium, and large clinically important differences on the UPDRS- Motor-as 2.5, 5.2, and 10.8 points respectively. These correspond to Cohen's  $d = 0.19, 0.39$  and  $0.81$  respectively. Current estimates assume  $N = 45$  participants randomized in 1:1:1 fashion to three conditions and a medium effect size (M-UPDRS difference = 5.2). We stipulate that relative to placebo if any treatment has a posterior probability  $> 0.70$  of conferring improvement (MDS-UPDRS-M difference  $> 0$ ) and a median posterior estimate of the effect size at least as large as an MDS-UPDRS-M difference of 2.5 (i.e. a small effect), that this treatment is eligible for continued investigation in a larger clinical trial. Under these assumptions,  $M = 1000$  Monte Carlo simulations using the normal approximation to the posterior distribution indicate that the proposed design will identify an effect of treatment 72% of the time.

## 14.3 Statistical analysis

Hypothesis 1.1. At least one active MSC group will demonstrate improved scores ( $\geq -5$ ) relative to placebo at 62 weeks follow-up. Generalized linear modeling will evaluate the MDS-UPDRS motor section as a function of treatment. Application of the decision-rules, discussed in the Sample Size Section, to the resulting posteriors will identify the candidate doses that warrant further investigation.

Hypothesis 2.1. Generalized linear modeling will characterize serious adverse reactions, significant worsening of general and motor functional state, activities of daily living, and peripheral immunologic responses. In each case, the subtraction of the posterior distribution for the treatment condition from the posterior distribution of the placebo condition will permit estimates of the posterior probability that the active condition is better than or equal to the control.

Hypothesis 2.2. Generalized linear modeling will estimate the improvement in motor function, disability, quality of life, non-motor symptoms, cognitive and behavioral symptoms as a function of treatment.

Hypothesis 3.1. Bayesian, multilevel structural equation modeling will evaluate the degree to which cytokines, chemokines, growth factors, and neurotransmitters transmit the effect of treatment to the MDS-UPDRS motor section at 62 weeks.

Hypothesis 3.2. Separate multilevel generalized linear modeling to account for correlations due to repeated observations within participants will evaluate the MDS-UPDRS motor section as a function of time and time-varying covariates, including kinetic parameters of  $\alpha$ Syn-PMCA in plasma and CSF before and after treatment.

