### 5.1 Outcomes

#### 5.1.1 Primary outcome

The primary goal of this trial is to select the safest and most effective number of repeat doses of allogeneic bone marrow-derived MSC with the aim to slow the progression of PD as determined by the change on the motor section of the MDS-UPDRS ( $\geq -5$ ) in each active treatment arm versus placebo between screening and 62 weeks follow-up.

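### The primary success bar is written as 5 motor points over placebo, but Hypothesis 1.1 is decided by a 2.5-point go rule, and the 72% is the chance of passing that go rule

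*Protocol*

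**What the plan says.** Four places give 5 points. The synopsis and 5.1.1 make the choice of regimen depend on a "change on the motor section of the MDS-UPDRS ( $\geq -5$ ) in each active treatment arm versus placebo". In 14.3, Hypothesis 1.1 reads "At least one active MSC group will demonstrate improved scores ( $\geq -5$ ) relative to placebo at 62 weeks follow-up", and 14.4 repeats it for the interim analysis at 40 weeks. I read the expression as a benefit of at least 5 points; how its sign is written is a separate matter.

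Section 14.2 says "sample size justification will focus on Hypothesis 1.1", but defines success differently. An arm is eligible for a larger trial if it has a "posterior probability $> 0.70$ of conferring improvement" (difference above 0) and "a median posterior estimate of the effect size at least as large as an MDS-UPDRS-M difference of 2.5", which the section calls a small effect. The planning effect is 5.2 points. Under these assumptions, 14.2 reports that "the proposed design will identify an effect of treatment 72% of the time".

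Section 14.3 ties the two together: "Application of the decision-rules, discussed in the Sample Size Section, to the resulting posteriors will identify the candidate doses that warrant further investigation".

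**The concern.** One hypothesis carries two bars that differ two-fold, and nothing says how they relate. An arm 3 or 4 points better than placebo would pass the 14.2 rule and be eligible for a larger trial. The same arm would fall short of the 5 points in 5.1.1 and in Hypothesis 1.1. Choosing a regimen is the trial's stated objective, so the description of the primary result should not be open to two readings.

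The 72% is exposed to the same confusion. Section 14.2 presents it as the justification for Hypothesis 1.1, so it can be taken as the chance of showing a 5-point benefit. The protocol gives no figure for that event.

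**Working it through.** **Inputs**

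- True benefit 5.2 points (14.2).
- 15 per arm, from 45 subjects randomized 1:1:1 (6.5, 14.2).
- SD: not stated. The pairs of points and Cohen's d in 14.2 imply it: 5.2/0.39 = 13.33, 10.8/0.81 = 13.33, 2.5/0.19 = 13.16.
- Flat prior and no covariate adjustment: assumed, since 14.2 states neither.
- Normal approximation to the posterior (14.2).

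**Step 1: reproduce the 72%**

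- SE of an arm-versus-placebo difference = 13.33 × √(2/15) = 4.87.
- Posterior probability of benefit above 0.70 needs an estimate above 0.524 × 4.87 = 2.55. The median criterion needs 2.5. The effective cut is the larger, 2.55.
- Chance of passing, one arm = Φ((5.2 − 2.55)/4.87) = 70.7%. With SD 13.16 (SE 4.80, cut 2.52) it is 71.2%.
- Monte Carlo SE with 1000 runs = √(0.71 × 0.29/1000) = 1.4 points, so 72% agrees with the go rule.

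**Step 2: a 5-point bar with the same inputs**

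- Posterior median at least 5, one arm: Φ((5.2 − 5)/4.87) = 51.6%. The 0.70 condition is then met automatically.
- Posterior probability of a benefit above 5 itself above 0.70, one arm: the cut is 5 + 2.55 = 7.55, and Φ((5.2 − 7.55)/4.87) = 31%.

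**Step 3: at least one of two arms, shared placebo group**

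Simulated with SD 13.33 and 1,000,000 draws per scenario:

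| True benefits | Go rule | Median at least 5 |
|---|---|---|
| 5.2 and 5.2 | 85% | 68% |
| 5.2 and 2.5 | 78% | 59% |
| 5.2 and 0 | 74% | 54% |

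**Step 4: how often the two bars disagree**

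The chance that one arm's estimate lies between 2.55 and 5 is the difference of the two pass rates:

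- True benefit 5.2: 70.7% − 51.6% = 19%.
- True benefit 2.5: Φ((5 − 2.5)/4.87) − Φ((2.55 − 2.5)/4.87) = 19%.
- True benefit 0: 30.0% − 15.2% = 15%.

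**The case against.** The strongest reply is that the protocol does say which rule decides. Directly after Hypothesis 1.1, 14.3 names the 14.2 rule as the one that identifies candidate doses, and no threshold, test or verdict is attached to 5 points anywhere. On this view 5 is the hoped-for effect, close to the planned 5.2, and 2.5 with 0.70 is the go threshold. A go threshold below the target effect is ordinary in a phase IIa selection trial, and 14.4 says the main worry is missing a real benefit.

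Much of this stands. A reader might infer that the dose decision itself is open and could be settled after the data are seen. The documents do not support that, because 14.3 fixes the rule for candidate doses. What stays open is how the primary outcome would be reported.

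A reader might also infer that the 72% is wrong and should be 52%. That does not follow either. The 72% reproduces for the rule it is stated with. The 52% rests on a median rule that the protocol does not contain, and it applies to one arm, whereas Hypothesis 1.1 speaks of at least one. It also carries little information: a bar of 5 beside a planning effect of 5.2 gives roughly 50% whatever the spread (53% at SD 8, 51% at SD 20).

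The reply does not dispose of the wording. The protocol never labels 5 as a target. It gives the planning effect separately as 5.2, and 5.1.1 says the selection is made "as determined by the change on the motor section of the MDS-UPDRS" with the 5-point figure attached. Nor can an SAP agree with both bars.

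**Conclusion.** The inconsistency is real, and it concerns the stated primary success criterion. Four places say 5 points, while the rule that decides Hypothesis 1.1 asks for a posterior median of 2.5 and a probability above 0.70. The 72% belongs to the second.

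In size: the go rule gives about 71% for one arm at a true 5.2. A 5-point criterion gives about 52% for one arm if read as a posterior median, 54 to 68% for at least one of two arms (go rule on that basis: 74 to 85%), and about 31% for one arm if read as a probability above 0.70 of exceeding 5. About 19% of trials at a true 5.2 leave an arm between the bars.

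These figures rest on the implied SD of 13.2 to 13.3, 15 evaluable subjects per arm, a flat prior and an unadjusted comparison. The unit of the 72% is not settled by arithmetic: one arm gives 70.7 to 71.2%, and at least one of two arms with true benefits of 5.2 and 0 gives 73.9 to 74.3%. Both are compatible with 72% given the simulation error.

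This should be corrected before unblinding. It does not put the design or the go rule in doubt.

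**What to change.** Use one success criterion. The simplest course is to make the 14.2 go rule that criterion in the synopsis, 5.1.1, Hypothesis 1.1 and 14.4, and to name 5.2 points as the planning effect only. Section 14.2 should add that the 72% is the chance of passing the go rule, and whether it is for one arm or for any arm. Report the posterior probability of a benefit of at least 5 points beside the go verdict, so that the larger effect remains visible.

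If 5 points is to remain the success criterion, define it as a posterior rule and restate the 72% for that rule and unit. The figure will be lower.

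Either course costs protocol and SAP wording. The first changes nothing in sample size, arms, visits or the go rule.

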| DURATION OF TREATMENT              | Each patient will receive 3 infusions of either placebo or MSC at a rate of 2 ml/min, followed by a 4-hour monitoring period.                                                                                                                                                                                                       |
| PRIMARY OUTCOME MEASURE(S)         | To select the safest and most effective number of repeat doses of allogeneic bone marrow-derived MSC with the aim to slow the progression of PD as determined by the change in the motor section of the MDS-UPDRS score ( $\geq -5$ ) in each active treatment arm versus placebo between baseline and 62 weeks follow-up.          |
| SECONDARY OUTCOME MEASURE(S)       | 
Aim 2. Assess safety, tolerability, and secondary measurements of clinical efficacy including; cognition, behavioral changes, motor function, disability, and QOL.
 
Aim 3. Explore putative mechanisms of action for the effect of MSCs.
                                                                               |
| SAMPLE SIZE CONSIDERATIONS         | Current estimates assume N = 45 participants randomized in 1:1:1 fashion to three conditions and medium effect size (MDS-UPDRS III difference = 5.2).                                                                                                                                                                               |

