## 6.5 Method of Assigning Subjects to Study Drug

Subjects will be assigned to any of the three treatment arms randomly on ratio 1:1:1 by computer table randomization method to yield a total of up to 45 randomized treated subjects; 15 subjects per arm. Screen failures or subjects who exit the study prior to the administration of the first treatment dose may be replaced with additional subjects, which could cause an overall number of subjects randomized to be greater than the 45 anticipated. However, no more than 45 subjects will be treated.

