| Clinical Assessment | Demographics, EKG, Specialty
labs*                            | X                         |                            |                  |                           |                          |                            |                          |                               |                               |                            |                               |                            |                                   |
|                     | Physical and neurological
examination. Meds review            | X                         |                            | X                | X                         | X                        | X                          | X                        | X                             | X                             | X                          | X                             | X                          | X                                 |
|                     | Vital Signs                                                      | X                         | X                          | X                | X                         | X                        | X                          | X                        | X                             | X                             | X                          | X                             | X                          | X                                 |
|                     | UPSIT & MOCA                                                     | X                         |                            |                  |                           |                          |                            |                          |                               | X                             |                            | X                             |                            | X                                 |
|                     | MDS- UPDRS, TUG, H&Y (OFF)                                       | X                         |                            |                  | X                         |                          | X                          |                          | X                             |                               | X                          | X                             |                            | X                                 |

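### The primary analysis names no baseline term, the response is a score in one section and a change in another, and neither adjusts for the screening OFF motor score

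*Protocol*

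**What the plan says.** - **Model.** Section 14.3, Hypothesis 1.1: "Generalized linear modeling will evaluate the MDS-UPDRS motor section as a function of treatment". The comparison is "relative to placebo at 62 weeks follow-up", and the decision rule of section 14.2 is applied to the resulting posteriors. Section 14.4 repeats the model for the interim look, with Hypothesis 1.1 set at 40 weeks. Neither section names a baseline term for this hypothesis. In the same section 14.3, Hypothesis 3.2 does name time and time-varying covariates.
- **Outcome.** The synopsis has progression "as determined by the change in the motor section of the MDS-UPDRS score", counted from baseline to week 62. Section 5.1.1 has the change "in each active treatment arm versus placebo between screening and 62 weeks follow-up".
- **Data.** The study schedule (row "MDS- UPDRS, TUG, H&Y (OFF") places the OFF motor score at screening and at weeks 9, 27, 40, 62 and 88. The Baseline visit (section 10.1.2) has imaging, blood, urine and lumbar puncture but no motor rating.
- **Size.** Section 6.5 gives "15 subjects per arm". Section 14.2 reports simulations that "indicate that the proposed design will identify an effect of treatment 72% of the time".

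**The concern.** Two things are unsettled for the analysis that drives the go decision. The first is the response: section 14.3 models a score, while the synopsis and section 5.1.1 describe a change. The second is the role of the pre-treatment score. The synopsis counts from a visit with no motor rating if its baseline means the Baseline visit, and no passage makes the screening score a covariate.

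This matters at 15 per arm because patients differ widely in motor score before treatment. Suppose the screening SD is about 13.3, as at week 62, and allocation does not balance on the screening score. The chance gap at screening between one active arm and placebo then has an SD of 13.33 × √(2/15) = 4.87 points, close to the 5.2-point target. With correlation r between screening and week 62, an unadjusted week-62 comparison carries r times that gap into the estimate. A change score subtracts the whole gap and so over-corrects by (1 − r) times it. Adjusting for the screening score removes the part that the score predicts. At stake are both error rates of the go rule: missing an effective arm and advancing an ineffective one.

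**Working it through.** **Inputs from the protocol**
- Patients per arm: 15 (section 6.5).
- Target difference: 5.2 points (section 14.2, "medium effect size (M-UPDRS difference = 5.2"), equated there with Cohen's d = 0.39. The implied SD is 5.2/0.39 = 13.33. The section's other pairs give 2.5/0.19 = 13.16 and 10.8/0.81 = 13.33.
- Go rule (section 14.2): posterior probability of benefit above 0.70 and posterior median of at least 2.5 points.

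**Assumption:** correlation r between the screening and week-62 OFF scores, range 0.5 to 0.8. The protocol does not give it.

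**Step 1: reproduce the 72%.** Take one active arm against placebo, a flat prior and the normal approximation.
- SE = 13.33 × √(2/15) = 4.87.
- Go cut = max(2.5, 0.5244 × SE) = max(2.5, 2.55) = 2.55.
- P(go | 5.2) = Φ((5.2 − 2.55)/4.87) = 70.7%. With SD 13.16 it is 71.1%.

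The Monte Carlo standard error at 1000 runs is √(0.72 × 0.28/1000) = 1.4 points, so this agrees with the stated 72%. The figure is reached without any credit for a baseline covariate. At zero effect the same arm passes with probability 30%.

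**Step 2: three analyses compared**
- Unadjusted week-62 score: SE = 13.33 × √(2/15)
- Change score: SE = 13.33 × √(2(1 − r)) × √(2/15)
- Adjusted for the screening score: SE = 13.33 × √(1 − r²) × √(2/15)

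The cut is 2.5 wherever 0.5244 × SE is below 2.5. False go is the probability that one arm with zero effect passes.

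| r | Analysis | SE | P(go at 5.2) | False go per arm |
|---|---|---|---|---|
| any | Unadjusted score | 4.87 | 70.7% | 30.0% |
| 0.5 | Change | 4.87 | 70.7% | 30.0% |
| 0.5 | Adjusted | 4.22 | 73.9% | 27.7% |
| 0.7 | Change | 3.77 | 76.3% | 25.4% |
| 0.7 | Adjusted | 3.48 | 78.1% | 23.6% |
| 0.8 | Change | 3.08 | 81.0% | 20.8% |
| 0.8 | Adjusted | 2.92 | 82.2% | 19.6% |

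Example, adjusted at r = 0.7: Φ((5.2 − 2.5)/3.48) = 78.1%, and at zero effect 1 − Φ(2.5/3.48) = 23.6%.

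Against the unadjusted score the SE falls by 1 − √(1 − r²), which is 13% at r = 0.5 and 40% at r = 0.8. Against the change score it falls by 1 − √((1 + r)/2), which is 13% at 0.5 and 5% at 0.8. The gain over change in P(go) is 3.2, 1.8 and 1.2 points at r = 0.5, 0.7 and 0.8. Allowing for the cost of estimating the covariate slope (SE × √(1 + 1/40)) changes the adjusted P(go) only to 73.6%, 77.8% and 81.9%.

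**Step 3: if 13.33 is really the SD of the change.** The protocol does not say which SD it is. Under this reading the change-score SE is 4.87 at any r, and the adjusted SE is 4.87 × √((1 + r)/2) = 4.22, 4.49 and 4.62. P(go) becomes 73.9%, 72.6% and 72.1% against 70.7%, a gain of 3.2, 2.0 and 1.4 points. The conclusion against a change score is almost the same.

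**Step 4: the other post-infusion visits.** With complete data, a repeated-measures model with arm-by-visit terms and unstructured covariance gives the same week-62 contrast as the single-visit adjusted model, so the gain is 0. With a fraction m missing at week 62, the variance is multiplied by about 1 − m·q², where q is the correlation between visits given screening. Under equal correlations among visits, q = (r − r²)/(1 − r²) = 0.33, 0.41 and 0.44 for r = 0.5, 0.7 and 0.8. With m of 10-20% the gain in P(go) is about 0.1 to 0.5 points.

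**The case against.** The strongest reply has three parts.

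1. Section 14.3 does not say that treatment is the only predictor. The synopsis and section 5.1.1 define the outcome as a change, so baseline enters the endpoint, and covariates are commonly left to a statistical analysis plan, which is not shown here. This largely stands. A reader might infer that the plan ignores the baseline score. The documents do not support that; they support only that the sections disagree on the response and that none names the covariate. What weakens the reply is that the protocol itself writes out the primary model and ties the go rule to it, and it lists extra predictors for Hypothesis 3.2.

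2. The larger gains use an unadjusted week-62 score as comparator. Against the change that the protocol defines, adjustment adds 1 to 3 points. This stands, and both comparisons are needed because the sections do not agree.

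3. The SD is back-calculated, and leaving baseline out of the sizing is conservative. Both are true. Step 3 shows that the first makes little difference against a change score; the second means that the 72% is not an error.

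Stronger readings are also tempting. One is that the trial throws away precision by not modelling its other visits. Step 4 shows that this does not hold for a week-62 contrast with complete data. Another is that patients without a week-62 score will be dropped, but no complete-case rule is stated and the 10% in section 6.4 is a screen-failure rate. A third is that randomisation is simple. Sections 6.5 and 14.1 say only that a computer table is used, which does not settle whether allocation is blocked or stratified.

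**Conclusion.** The point holds as a matter of specification and efficiency; it does not invalidate the design. The response and reference visit are described inconsistently across the synopsis, section 5.1.1 and section 14.3, and the one available pre-infusion OFF motor score is not named as a covariate. If section 14.3 is applied as worded to the raw score, adjustment would raise P(go | 5.2) from 70.7% to 73.9-82.2% and cut the false-go rate per arm from 30% to 27.7-19.6%. If a change score is analysed, the benefit is 1.2 to 3.2 points of P(go).

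These sizes rest on an assumed correlation of 0.5 to 0.8, an SD of 13.33 inferred from the stated effect sizes, equal SDs at screening and week 62, a flat prior, and 15 evaluable patients per arm. In every case computed, adjustment does at least as well as either alternative on both error rates.

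**What to change.** - In section 14.3, state that each active arm is compared with placebo on the OFF MDS-UPDRS III at week 62, adjusted for the screening OFF motor score. In section 14.4, state the same for the interim at week 40, the visit named in its Hypothesis 1.1.
- Make screening the reference visit in both the synopsis and section 5.1.1, since the Baseline visit has no motor rating. If the outcome continues to be called a change, keep the screening score as covariate: the treatment contrast is then the same as for the adjusted score.
- State that the go rule of section 14.2 is applied to the adjusted posterior.
- Rerun the simulation with that model, give the assumed SD and correlation, and report P(go) at zero effect as well as at 5.2 points.
- Optionally, include the other post-infusion visits in a repeated-measures model as a modest safeguard against missing week-62 scores.

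The cost is protocol wording and one rerun of the simulation. No visit, assessment or patient is added. If a statistical analysis plan already names the covariate, only the protocol wording and the sizing text need aligning.
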